### 2.2. Participants

The following inclusion criteria will be applied: being diagnosed with idiopathic Parkinson's disease by a neurologist based on definitive evidence of responsiveness to levodopa at the start of the disease and the history of progressive hypokinesia with asymmetric onset. PD will be diagnosed based on Parkinson's Disease Society Brain Bank (PDSBB) criteria, as described in Hughes et al. (1992): age between 40 and 70 years, with no distinction for sex, schooling level or other sociodemographic characteristics; disease staging between 1.5 and 3, according to the modified Hoehn and Yahr scale (Hoehn and Yahr, 1998); undergoing regular pharmacological treatment with levodopa (equivalent dose > 300 mg) or taking antiparkinsonian medication, such as anticholinergics, selegiline, dopamine agonists, and COMT (catechol-O-methyl transferase) inhibitors for at least 4 weeks prior intervention; score of more than 24 points on the Mini-Mental State Examination (Folstein et al., 1975); not exhibiting other associated neurological diseases; and no musculoskeletal and/or cardiorespiratory changes that could compromise gait. The exclusion criteria will be diagnosis of atypical Parkinson's disease; neuropsychiatric comorbidities; convulsions, metal clips and/or pacemaker; deep brain stimulation implant; history of epilepsy; neurosurgery; traumatic brain injury; alcohol abuse or drug dependency; associated diseases of the peripheral or central nervous system; undergoing physical therapy at another location; inability to walk 10 meters; presence of important dyskinesia that prevents the participant from sitting in a chair; abnormal and persistent increase in systemic blood pressure before or during training, after three measurements taken 5 min apart-Cut-off: systolic blood pressure ≥ 140 mm Hg and/or diastolic ≥ 90 mm Hg (Malachias et al., 2016); not understanding any of the training protocol stages; chemical scalp treatment within the previous 30 days, and experiencing severe pain and/or discomfort that precludes performing the proposed activities.

History of falls in the last 12 months will be used to classify individuals into “non-fallers” (number of falls ≤ 1) or “recurrent fallers” (number of falls ≥ 2). Freezing of gait episodes will be screened and classified according to the dual-task screening questionnaire (Strouwen et al., 2014).

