### 2.4. Randomization and Blinding

Participants will be randomly allocated, using an online generator (www.random.org), into two groups (1:1): CG) tDCS active + gait training; EG) tDCS active + gait training + dual-task. This sequence will be performed independently and remotely by a blinded investigator, who will have no knowledge of other study procedures. Randomization will be concealed until group allocation and stratified by subgroup with or without freezing of gait (FOG).

The concealed allocation process will be conducted using sequentially numbered sealed opaque envelopes. The outcome assessors, trialists and patients will be blinded to the procedures.

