### 2.6. Screening

Study participants will be submitted to screening and an initial visit before being assessed for primary and secondary outcomes. A structured evaluation will be carried out, including sociodemographic data; time since diagnosis; disease severity according to the modified Hoehn and Yahr Clinical Staging Scale (Hoehn and Yahr, 1998; Goetz et al., 2004); medication doses used; levodopa equivalent daily dose (LEDD); symptoms of depression and anxiety, measured by the Hospital Anxiety Depression (HAD) scale; freezing of gait, assessed by the Freezing of Gait Questionnaire (FOG-Q) (Giladi et al., 2009); and type of disease, classified as akinetic-rigid, tremulant or mixed. Although of tremor-dominant and nontremor-dominant subtypes are the most comonly system used to defining Parkinson's disease subtypes, the participant's classification as postural instability gait disorder (PIGD) phenotype (or akinetic-rigid) has been used to specify a nontremor-dominant subtype (Marras, 2015). In this study, the participant's classification for PIGD score will be described based on “walking and balance” and “freezing” items of part II of Movement Disorder Society Unified Parkinson's Disease Rating Scale scores (MDS-UPDRS), and the “gait”, “freezing of gait” and “postural stability” items of part III of MDS-UPDRS scores (Jankovic et al., 1990). TD/PIGD scores will be used for all patients and calculate by dividing mean tremor subscores (2.10, 3.15a, 3.15b, 3.16a, 3.16b, 3.17a, 3.17b, 3.17c, 3.17d, 3.17 and 3.18) by mean PIGD subscores (2.12, 2.13, 3.10, 3.11 and 3.12) (Stebbins et al., 2013). Values equal to 1.15 classifiles the patient as TD subtype, whereas values equal to 0.90 represent PIGD. The patient will be classified as indeterminate subtype if the ratio between mean TD and mean PIGD valeus will be between 0.90 and 1.15 (Stebbins et al., 2013). The Mini-Mental State Examination (MEEM) will be applied in order to characterize the sample (Folstein et al., 1975). We will investigate lateral dominance aspects using the Edinburgh Handedness Inventory (Oldfield, 1971), and collect anthropometric data such as head circumference, inter-tragus and nasion-inion distance, height, weight and body mass index (BMI).

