### 2.7. Outcomes

The primary outcome will be functional mobility, measured using the Timed Up and Go test (Podsiadlo and Richardson, 1991), to stand up from a chair at the command: “Walk 3 meters, walk along a demarcated course, turn around and walk back to the chair, then sit down”. For secondary outcomes, the following instruments will be used to assess executive function: (1) Wisconsin Card Sorting Test (WCST) to assess planning, cognitive flexibility, working memory, monitorization, inhibition of perseverations, and aspects related to executive function (Heaton and Staff, 1993); (2) Stroop Test, to assess selective attention, inhibition, cognitive flexibility, processing speed, fluid intelligence and the semantic system (Lezak et al., 2004, Strauss et al., 2006); (3) Trail Making Test (TMT), to evaluate the ability to draw lines between consecutive numbers from 1 to 25 (Bowie and Harvey, 2006); (4) Verbal Fluency Test to assess semantic and phonemic fluency in 1 min (Brucki and Rocha, 2004); and (5) Montreal Cognitive Assessment(MoCA), to evaluate overall cognitive and executive function (Van Uem et al., 2016).

The following scales will be used to assess motor function: (1) Dynamic Gait Index (DGI), to assess eight aspects of gait as well as dynamic balance (Shumway-Cook et al., 2000); (2) 10-meter walk test, to estimate gait speed by recording the average time the patient takes to cover a distance of 10m in three attempts (Peters et al., 2013); (3) Borg Scale, to guide physical activity intensity level and measure perceived exertion during session training (Borg, 1982); (4) Sit-to-stand (STS) test; (5) Kinematics of Gait, to analyze movement using the Qualisys Motion Capture System (Qualisys Medical AB, 411 13, Gothenburg, Sweden). This system records the spatio-temporal variables of gait, as well as the angular variations of the hip, knee and ankle joints; (6) MiniBESTest, to measure aspects of static and dynamic balance (Franchignoni et al., 2010); (7) Revised Movement Disorder Society-Sponsored Revision of the Unified Parkinson's Disease Rating Scale (MDS-UPDRS), to assess motor function (Goetz et al., 2008); and (8) Short FES-I, to measure the level of confidence in performing daily activities, in addition to identifying fear of falling and possible social isolation (Kempen et al., 2008). All the instruments used to assess the primary and secondary outcomes are described in Table 1.

**Table 1 T1:** Primary and secondary outcome measures.

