### 2.11. Data Analyses

The Statistical Package for the Social Sciences (SPSS), version 27.0, will be used in data analysis and a 5% alpha (*P* < 0.05) will be established.

The groups will be compared using the Student's *t*-test or Mann-Whitney test, for continuous variables, or the chi-squared test for categorical variables, according to the normality distribution, analyzed using the Shapiro-Wilk test. The primary outcome will be examined with a repeated measures split-plot ANOVA, with one dependent and two independent variables: one intragroup (time, with 3 levels: T0, T1 and T2), and one intergroup (a group with two levels: CG and EG) using Sidak's *post hoc* test. Analyses of covariance (ANCOVA) will be used to identify significant intergroup differences applying T0 scores as covariables. Linear regression will be used to identify response predictors. The independent variables will be group and clinical response, that is, the minimal clinically important difference (MCID). An intention to treat analysis will be conducted.

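### Randomisation is stratified by freezing of gait, but neither the stated ANOVA nor the ANCOVA includes it, so available precision may be forgone

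*Protocol article*

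**What the plan says.** Section 2.4 (Randomization and Blinding): "Participants will be randomly allocated, using an online generator (www.random.org), into two groups (1:1"). Allocation is further "stratified by subgroup with or without freezing of gait (FOG"). No blocking within strata is described.

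Section 2.7 (Outcomes): "The primary outcome will be functional mobility, measured using the Timed Up and Go test".

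Section 2.11 (Data Analyses): "The primary outcome will be examined with a repeated measures split-plot ANOVA, with one dependent and two independent variables". The two are then listed: "one intragroup (time, with 3 levels: T0, T1 and T2), and one intergroup (a group with two levels: CG and EG"). An ANCOVA for between-group differences follows, with T0 scores as the only covariates named.

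FOG is measured in two places. Section 2.2 (Participants): "Freezing of gait episodes will be screened and classified according to the dual-task screening questionnaire". Section 2.6 (Screening): "freezing of gait, assessed by the Freezing of Gait Questionnaire (FOG-Q"). Section 2.4 does not say which of them defines the stratum.

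The Introduction lists freezing of gait among the factors that seem to influence response to therapy.

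**The concern.** Stratifying on a prognostic factor makes the arms alike on it, so the true sampling variance of the treatment contrast no longer contains that factor's share. A model without the factor still counts its variance as error. The reported standard error is then larger than it should be, the test rejects too rarely under the null, and power is lost.

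The omission cannot be put down to condensation. Section 2.11 counts and names the terms of the primary model, and FOG is not among them. Small losses are relevant because the Limitations section itself says the sample size may be limited.

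**Working it through.** **The plan's own figure.** Section 2.10 gives 46 patients for 90% power at p < 0.05 and 56 recruited, an allowance of 10/56 = 17.9% for losses. It states no difference, SD or correlation, so 46 cannot be reproduced forwards. Solving backwards for two means (two-sided 5% assumed), n per arm = 2(1.960 + 1.282)²/d². With n = 23 this gives d² = 21.02/23 = 0.914 and d = 0.956. The exact t-test needs d = 0.98.

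**Assumptions for the check (none is in the article).** N = 46; half the patients with FOG; within-stratum SD of 1; correlation 0.7 between visits; arms balanced within FOG strata; treatment effect 0.6 SD at T1 and T2. Let g be the FOG difference in TUG at every visit, and k the extra FOG difference at T1 and T2. So k is the FOG effect on change.

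**Closed form, change contrast (group-by-time).** Within-stratum variance of T1 − T0 is 2(1 − 0.7) = 0.60. A constant g cancels in the subtraction. Leaving FOG out adds k²/4.

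- k = 0: SE = √(0.60 × 4/46) = 0.228, with or without FOG.
- k = 0.5: SE = √(0.6625 × 4/46) = 0.240, a ratio of √(0.6625/0.60) = 1.05.

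**Closed form, ANCOVA of T1 on T0.** With FOG in the model, residual variance is 1 − 0.7² = 0.51. Without it, residual variance is Var(T1) − Cov²/Var(T0), where Var(T0) = 1 + g²/4, Var(T1) = 1 + (g+k)²/4 and Cov = 0.7 + g(g+k)/4.

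- g = 1, k = 0: 1.25 − 0.95²/1.25 = 0.528, ratio √(0.528/0.51) = 1.02.
- g = 1, k = 0.3: 1.4225 − 1.025²/1.25 = 0.582, ratio 1.07.
- g = 1, k = 0.5: 1.5625 − 1.075²/1.25 = 0.638, ratio 1.12.

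**Simulation, 6,000 trials per setting.** The Monte Carlo standard error of one power figure is about √(0.77 × 0.23/6000) = 0.5 points. Power without → with the FOG terms:

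| FOG effect | Group-by-time | ANCOVA on T0 |
|---|---|---|
| none (g = 0, k = 0) | 77.5% → 77.3% | 78.6% → 78.8% |
| g = 1, k = 0 | 76.4% → 76.3% | 77.6% → 78.6% |
| g = 1, k = 0.3 | 75.4% → 76.2% | 74.7% → 78.9% |
| g = 1, k = 0.5 | 73.4% → 76.3% | 70.5% → 78.5% |

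The simulated standard errors agree with the formulas. For the change contrast they are 0.227 either way at k = 0, and 0.239 against 0.227 at k = 0.5. For the ANCOVA they are 0.215 against 0.212 at k = 0, and 0.237 against 0.212 at k = 0.5 (0.237/0.212 = 1.118).

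**Type I error without FOG.** At g = 1, k = 0.5 it is 4.4% for group-by-time and 3.6% for the ANCOVA: conservative, not inflated.

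**If the arms are not balanced on FOG.** At g = 1, k = 0.5, type I error without FOG is 4.9% for both tests, so the unadjusted standard error is correct. Adjustment still gains power: 72.3% → 75.5% for group-by-time and 69.3% → 78.3% for the ANCOVA.

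**The case against.** The strongest objection concerns the primary analysis itself. If the group-by-time interaction is the decisive test, a stable FOG difference is already removed by the within-person comparison and there is nothing to recover. This stands. Any loss on that test needs FOG to predict change in TUG, and it is then small. The Introduction makes such a link plausible but does not quantify it, and it does not say that this is why allocation was stratified.

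The effect size also matters. At the 0.956 SD back-solved from the stated sample size, ANCOVA power is about 98% to 99% either way under the same assumptions, a difference of about one point at most. The loss is visible only if the true effect is smaller than the one planned for.

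Conservatism further requires that stratification really balances FOG, and no blocking is stated. Without balance, only the efficiency gain is forgone.

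A reader might infer that the error bars in the primary analysis are certainly too wide. The article does not support that, because the result depends on which ANOVA term is read and on an unknown FOG-TUG association. The group main effect does lose more: with a 1 SD level effect alone its power is 22.9% without FOG and 31.9% with it, and type I error is 2.7%. But that term averages in the pre-treatment T0 visit, so it is not a natural test of treatment, and the article does not say that it decides the trial.

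A reader might also infer that Sections 2.2 and 2.6 contradict each other on FOG. They can be read as one questionnaire classifying patients and the other describing severity. What remains is that the stratum's source is not named.

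Adjustment for stratification factors is often left to an analysis plan. That carries less weight here, because the article writes the model terms out.

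**Conclusion.** The point holds as one of efficiency and consistency, not of validity. The stratification factor is missing from both written-out models. No bias and no excess false positives follow.

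Under the stated assumptions, the cost ranges from nothing (FOG unrelated to TUG, or the group-by-time test with a constant FOG difference) to about 3 points of power for group-by-time and about 8 points for the ANCOVA, whose standard error is then about 12% too wide. The upper ends need a 1 SD FOG difference in level and a further 0.5 SD in change. These figures illustrate a range and are not estimates for this trial, since the article supplies none of the inputs. It is a minor point, worth correcting because the correction is nearly free.

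**What to change.** - In every ANCOVA, add the FOG stratum, as used at randomisation, as a fixed factor beside the T0 score. Cost: one error degree of freedom.
- In the split-plot ANOVA, add FOG and FOG-by-time. A FOG main effect alone leaves the group-by-time test unchanged. With 46 patients, the between-subject error degrees of freedom go from 44 to 43 and the within-subject ones from 88 to 86.
- State in Section 2.4 whether the classification in Section 2.2 or the questionnaire in Section 2.6 defines the stratum, and analyse the stratum as randomised.

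No new data are needed. The change should be fixed before outcome data are examined.

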## Abstract

Patients with Parkinson's disease (PD) have difficulties while performing dual-task activities, a condition present in everyday life. It is possible that strategies such as transcranial Direct Current Stimulation (tDCS) can be associated with motor training enriched with dual-task training to improve the performance of two concurrent tasks. Currently, it is unclear whether specific tasks and clinical conditions of PD patients have different results after the intervention. Therefore, the proposed randomized controlled trial will examine task-dependency in enhancing the effects of tDCS-linked rehabilitation training on PD and the relationships between baseline outcomes in responders and non-responders to therapy. Fifty-six patients with Parkinson's disease will be recruited to participate in this controlled, double-blind randomized multicentric clinical trial. Patients in modified Hoehn & Yahr stage 1.5–3, age between 40 and 70 years will be included. Subjects will be randomly assigned to an experimental group (EG) and a control group (CG). The EG will perform treadmill gait training associated with dual task exercises+tDCS, while the CG will only engage in treadmill gait training+tDCS. Blinded testers will assess patients before and after 12 intervention sessions and after a 4-week follow-up period. All patients will undergo a screening and an initial visit before being assessed for primary and secondary outcomes. The primary outcome measure is functional mobility measured by Timed Up and Go Test. Secondary outcomes include cognitive function, participation, motor function and body function and structure. This study will evaluate the effectiveness of an intervention protocol with tDCS, dual-task training and gait training in patients with PD. The study will also highlight the clinical factors and variability between individuals that could interfere in the training of a specific task and influence the therapeutic effect.

**Clinical Trial registration**: www.ClinicalTrials.gov, identifier NCT04581590.

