## 2. Materials and Methods

### 2.1. Design

This is a controlled, double-blind randomized multicentric clinical trial, in line with the Standard Protocol Items Recommendations for Interventional Trials (SPIRIT) guideline (Chan, et al.), Figure 1. This project was approved by the Institutional Research Ethics Committee (30668420.7.0000.5188) and will be conducted according to the 1964 Declaration of Helsinki (Rickham, 1964). The trial was prospectively registered with the public platform clinical trials registry (www.clinicaltrials.org).

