#### 2.9.3. Dual-Task Training Protocol (DTTP)

The dual-task training protocol (DT) will consist in cognitive exercise categories: verbal fluency, mental screening tasks, discrimination, decision-making and reaction time tasks, which will be associated to treadmill gait training (Sousa et al., 2016). Verbal commands will focus on the following: (1) large strides; (2) heel strike; (3) raising the knees while walking (Kelly et al., 2012).

DT will be conducted using activities with three levels of difficulty (Tables 2–4), such as (i) mental screening tasks involving addition and subtraction, such as counting backwards from 100 and subtracting 3 or 7, while walking; (ii) verbal fluency tasks in which the participant is asked to name items that start with a particular letter or have a common characteristic (farm animals, words with the letter A, B, C, etc) while walking; (iii) discrimination and decision-making tasks, such as saying YES when the word “strawberry” is heard and NOTHING when no fruit is heard; (iv) fastening buttons and a zipper while walking; (v) Looking down and then up while walking; (vi) walking with head turns associated with motor or cognitive disorders; (vii) dual-task of carry a tray while walking (Mehrholz et al., 2015). Participants will only evolve from one level to the next when performance on the previous level is free of error. Thus, progression toward better performance of both the participant and the task will be based on the time that the participant will spend walking on the treadmill, i.e., increasing the walking speed or time on the treadmill in each block, performing the greatest number of words, presenting greater accuracy in decision-making, and reducing response time (Strouwen et al., 2014). At the end, participants will be asked to report the functional difficulties experienced during DT training.

**Table 2 T2:** Dual-task training at difficulty level 1.

**Task**	**Task description**	**Outcome measurement**	**Task limitations**
Counting backwards from 100	Subject walks while counting backwards from 100	- Number of calculations concluded. - Number of incorrect calculations. - Gait speed.	Depending on ability, may be more difficult for some participants than others.
Walking while carrying a tray with only one empty glass	The subject walks while carry a tray with one empty glass	- Gait speed. - Number of stops.	Involving the upper limbs may affect gait pattern. Difficulty depends on the amount of water in the glass.

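### The trial is labelled double-blind with patients and trialists blinded to the procedures, but the arms differ only in overt dual tasks, so it can be assessor-blinded at most

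*Protocol article*

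**What the plan says.** Section 2.1 (Design) opens with the label: "This is a controlled, double-blind randomized multicentric clinical trial". The Abstract uses the same label. Section 2.4 (Randomization and Blinding) names three masked groups and what they are masked to: "The outcome assessors, trialists and patients will be blinded to the procedures". The term trialists is not defined anywhere in the article.

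Section 2.4 defines the arms as follows: "CG) tDCS active + gait training; EG) tDCS active + gait training + dual-task". Section 2.9.2 repeats this contrast and gives the control group no substitute task.

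Section 2.9.3 and Tables 2–4 set out what the experimental arm does on the treadmill. One example is "counting backwards from 100 and subtracting 3 or 7, while walking"; others are carrying a tray, naming words, fastening buttons and moving coins between pockets. Progression between difficulty levels depends on performance: "Participants will only evolve from one level to the next when performance on the previous level is free of error". The same section ends by asking about the training: "At the end, participants will be asked to report the functional difficulties experienced during DT training".

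The Abstract separately commits to blinded assessment: "Blinded testers will assess patients before and after 12 intervention sessions and after a 4-week follow-up period".

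**The concern.** A double-blind label tells readers that neither the patient's nor the therapist's expectation can differ between arms. Here it would carry from the Abstract and Design section into the trial report. If patients and treating staff know the procedure, any outcome that patients rate themselves can move with expectation, and the reported label would hide this. The label also bears on how a between-group difference on an effort-dependent performance test should be read. What is at stake is the strength of claim the trial may make, chiefly for its patient-reported secondary outcomes.

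**Working it through.** The point rests on no figure in the plan, so the check sets the article's statements side by side.

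**1. Is any component masked by a sham?** No. Section 2.4 gives active tDCS to both arms. The stimulation does not differ between arms, so there is nothing in it to mask.

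**2. What differs between arms?** Only the dual-task exercises (sections 2.4 and 2.9.2). No attention-matched or placebo task is described for the control arm.

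**3. Can patients be blinded to that difference?** No. An experimental patient subtracts aloud, carries a tray or fastens buttons while walking; a control patient walks. Section 2.2 also excludes people who do not understand the stages of the training protocol, so patients are expected to understand the very procedure they are said to be blind to. The object of the blinding sentence in section 2.4 is the procedures, not the study hypothesis.

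**4. Can the staff who deliver training be blinded?** No. Moving up a level requires an error-free performance, so someone must watch and score the tasks. In Table 4 a researcher reads out the fruit names to which the patient responds.

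**5. Can others be blinded?** Yes. Outcome assessors can be, and the article says twice that they are (Abstract and section 2.4). Investigators who do not treat can be as well, if that is what trialists means.

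**6. Which outcomes are affected?** Table 1 lists these secondary instruments:

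| Domain | Instruments | Count |
|---|---|---|
| Cognitive function | WCST, Stroop, TMT, Verbal Fluency, MoCA | 5 |
| Motor function | DGI, 10MWT, Borg, STS, gait kinematics, MiniBESTest, MDS-UPDRS II and III | 7 |
| Participation | Short FES-I | 1 |
| Total | 5 + 7 + 1 | 13 |

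- Short FES-I is clearly patient-reported: section 2.7 describes it as measuring confidence and fear of falling. It is the only instrument in its domain.
- Borg measures perceived exertion, which is the patient's own rating, although section 2.7 also uses it to guide training intensity.
- MDS-UPDRS part II is taken here, as an assumption, to rest at least partly on patient report. The article does not say so.

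The count is therefore 1 of 13 on the strictest reading and 3 of 13 on the widest.

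**7. And the primary outcome?** TUG is a timed performance test (section 2.7). A blinded assessor removes bias from the rater. It does not remove any effect of the patient's own knowledge on effort.

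**The case against.** The strongest defence is that assessor blinding is feasible and stated twice, that the primary outcome is a performance test taken by a blinded tester, and that a journal article need not describe how assessors are kept apart from trainers. All of that stands, and it limits the point to the label and the self-reported secondaries.

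Two further arguments have some force. Since trialists is undefined, it may mean non-treating investigators, who can be blinded. And since both arms receive active tDCS with treadmill training, patients might be kept unaware of the hypothesis or of which arm is experimental. Neither rescues the sentence in section 2.4: the treating staff still cannot be blinded, and patients are said there to be blinded to the procedures, not to the hypothesis.

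A reader might be tempted to infer more than the article supports:

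- **That assessor blinding is unprotected.** The article does not say that assessors are separate from trainers, but such safeguards are operational detail that the full protocol may hold. Their absence here is no contradiction.
- **That the dual-task difficulty question unmasks assessors.** Section 2.9.3 does not say who asks it, or whether the end means the end of a session or of the course. Nothing places it at an assessment visit. Only experimental patients could answer it, so keeping it away from assessors is a sensible precaution, but no breach is shown.
- **That TUG relies on a rater's stopwatch.** The article does not state the timing method.
- **That the whole trial is open-label, or that self-reported outcomes cannot support any efficacy statement.** With blinded assessors the first is too strong. For the second, labelling those outcomes as unblinded is enough.

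**Conclusion.** The point holds as a contradiction within the article. The stated blinding of patients to the procedures, and of trialists if the term includes treating staff, cannot be reconciled with the arms as described; double-blind is therefore the wrong label. Blinding of outcome assessors, and of any non-treating investigators, remains possible.

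The consequence is moderate. It falls mainly on the self-reported secondaries: one instrument for certain, and up to three of 13 if Borg and MDS-UPDRS part II are counted. Because Short FES-I stands alone, the whole Participation domain is affected. TUG keeps its protection from rater bias but not from effort linked to patients' knowledge of their arm. The direction and size of any bias cannot be derived from the article, and no sample-size or analysis figure changes.

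The conclusion assumes that the control arm has no undescribed matching task, since none appears in sections 2.4 or 2.9.2.

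**What to change.** 1. Replace double-blind with assessor-blinded in the Abstract and section 2.1, and revise the blinding sentence in section 2.4 to match.
2. In section 2.4, state who is masked to what. Define trialists, state that the staff delivering training are not blinded, and say whether patients are masked only to the hypothesis.
3. Identify Short FES-I, Borg and, to the extent that it is patient-reported, MDS-UPDRS part II as unblinded when they are interpreted and reported.
4. State in section 2.9.3 that the dual-task difficulty report is collected by staff who do not assess outcomes. It need not be delayed until after follow-up, which would only weaken recall.

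The cost is a few sentences and one staffing rule for a single question. The design, sample size and training are unchanged. The downside is that the stated blinding becomes less favourable than the present label.
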